## Abstract

**Background:**

Obesity is a public health concern in many countries due to its increasing prevalence. Euiiyin-tang is an herbal medicine formula often used as a clinical treatment for obesity. It acts to eliminate humidity and purify the blood, the causes of obesity identified by the theoretical framework of Korean medicine. The purpose of this study is to evaluate the efficacy and safety of Euiiyin-tang in treating obesity.

**Methods/design:**

This study is a randomised, double-blinded and placebo-controlled, multicentre trial. It has two parallel arms: the Euiiyin-tang group and the placebo group. A total of 160 obese adult women will be enrolled in the trial. The participants will be randomly divided at a 1:1 ratio at visit 2 (baseline). The participants will be administered Euiiyin-tang or placebo for 12 weeks. The primary endpoint is the change in weight occurring between baseline and post-treatment. The secondary outcomes include average weight reduction, changes in body fat, waist and hip circumferences, body mass index, and lipid profile, and the results of questionnaires such as the Korean version of Obesity-related Quality of Life, the Korean version of Eating Attitudes Test, the Social Readjustment Rating Scale, and the Stress Reaction Inventory.

**Discussion:**

The present study will provide research methodologies for evaluating the efficacy and safety of Euiiyin-tang in patients with obesity. In addition, it will provide evidence of correlation between obesity and Sasang constitutional medicine.

**Trial registration:**

ClinicalTrials.gov, NCT01724099. Registered on 2 November 2012.

**Electronic supplementary material:**

The online version of this article (doi:10.1186/s13063-017-2039-8) contains supplementary material, which is available to authorized users.

## Background

Obesity is defined as a modern disease, associated with diseases such as diabetes mellitus, hyperlipidaemia, and hypertension [1]. The prevalence of obesity (body mass index (BMI) ≥25) in Korean adults is 30.6% according to the third National Health and Nutrition Survey report [2]. Recent epidemiologic data show that the prevalence of obesity has increased, rising from 26.7% in 1998 to 30.9% in 2009 [3]. Consequently, the risk of mortality from coronary heart disease and haemorrhagic stroke mortality has increased [4]. The socioeconomic burdens associated with people who are overweight and/or obese are rising, with a cost of 1787 million US dollars in Korea in 2005 [5]. With the need for anti-obesity agents increasing, it is reported that agents such as sibutramine and rimonabant can cause adverse effects [6]. However, herbal medicine has attracted public attention due to the perception that it has fewer adverse effects.

Euiiyin-tang is a Korean medicine formula. It consists of seven herbs: *Ephedra sinica Stapf* (1.33 g), *Angelica gigantis Radix* (1.33 g), *Atractylodis rhizoma alba* (1.33 g), *Coicis Semen* (3.33 g), *Cinnamomi cortex* (1.00 g), *Paeoniae radix alba* (1.00 g), and *Glycyrrhiza uralensis* (0.67 g).

The primary constituent herbs of Euiiyin-tang have effects on obesity-related factors. Euiiyin (*Coicis Semen*) inhibits reactions of dihydroxyphenylacetic acid (DOPAC), 5-hydroxytryptamine (5-HT), and 5-hydroxyindoleacetic acid (5-HIAA) in the hypothalamus induced by fasting stress [7]. Consequently, Euiiyin helps to reduce hunger caused by dietary restrictions. In addition, Euiiyin has been reported to decrease total cholesterol and triglycerides in blood lipids [8, 9]. Ma-Huang (*Ephedra sinica Stapf*) has been frequently used in the treatment of obesity. Ma-Huang significantly decreases blood glucose, triglyceride, and free fatty acid levels in obese mice, and it has also been shown to reduce BMI, fat percentage, and total cholesterol and triglyceride levels in human studies [10, 11]. Baekchul (*Atractylodis rhizome alba*) inhibits corticosterone increase induced by fasting stress [12].

The effects of Euiiyin-tang include eliminating humidity, purifying blood, and relieving arthralgia according to the theoretical frameworks of Korean medicine [13, 14]. Korean medicine describes the cause of obesity as dampness-phlegm, which refers to the congestion of body fluids [15]. Euiiyin-tang helps to remove dampness-phlegm and circulate body fluids; therefore, it is suitable as a treatment for weight loss.

Sasang constitutional medicine is recognised as a distinct field of Korean medicine separate from that of traditional Chinese medicine. Sasang constitutional medicine divides human beings into four separate categories, or constitutions, based on their physiological characteristics. The prevalence of both general and abdominal obesity is highest among one of these constitutions, the Taeum-in. In addition, members of Taeum-in have a lower basal metabolic rate (BMR) [16, 17]. Sasang constitutional medicine has matched herbal medicines to each constitutional type. Euiiyin-tang contains Euiiyin (*Coicis Semen*) and Ma-Huang (*Ephedra sinica*), two herbs typically matched to Taeum-in [18]. We will examine the Questionnaire for Sasang Constitution Classification II (QSCCII) to identify whether Euiiyin-tang has a significant effect for Taeum-in or not [19, 20]. However, QSCCII was not considered as a primary outcome measure in the study, as it is not yet highly validated.

Euiiyin-tang has been frequently used in obesity treatment in Korean clinics and hospitals. A previous animal study revealed the weight loss effects of Euiiyin-tang; however, upon checking trial registries and a systematic review on the subject, human studies examining the effects of Euiiyin-tang on obesity have not been reported [21]. It has been proved, however, that Euiiyin-tang decreases body weight, blood lipids, and insulin levels in high-fat diet-induced obese mice [22].

The evidence on whether Euiiyin-tang affects weight loss is still insufficient; therefore, it is necessary to conduct clinical trials on this medicine. To address this issue, we designed a randomised, placebo-controlled clinical trial to evaluate the efficacy and safety of the pharmacological intervention, Euiiyin-tang, for weight loss in adult female Korean patients with obesity. We also want to verify the correlation between obesity and Sasang’s Taeum constitution.

## Methods/design

### Study design

The present study is a randomised, double-blinded, parallel-group, placebo-controlled multi-centre trial taking place at the following three hospitals: Gachon University Gil Medical Center in Incheon, Seoul St. Mary’s Hospital, and Sangji University Korean Medicine Hospital in Wonju. Participants will be outpatients of these institutions. Any participant fulfilling the eligibility criteria will be included in the study. This study will have two arms: the Euiiyin-tang treatment group and the placebo treatment group. Figure 1 presents an overview of the trial. Protocol amendments are not expected. However, if necessary, any modification to the protocol will be reported to the entire investigational team through a conference. All changes will be included in the final manuscript prior to journal submission.

**Fig. 1 Fig1:**
[figure not shown]
Flow chart of the Euiiyin-tang clinical trial

### Study objectives

The main objectives of the present study are (1) to evaluate the efficacy and safety of Euiiyin-tang in obese Korean female adults and (2) to detect the correlations between obese participants and the Taeum classification of Sasang constitutional medicine.

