2.1. BMI 30 kg/m^2^ or over
2.2. Obese patients, BMI 27–29.9 kg/m^2,^ who have more than one of the risk factors such as hypertension, diabetes, and hyperlipidaemia, and each of the conditions shall be subject to the following standards.
2.3. Hypertension: Patients under adequate treatment after being diagnosed with hyperlipidaemia (BMI 27–29.9 kg/m^2^) and with their blood pressure adjusted (satisfying all the conditions of systolic blood pressure (SBP) ≤145 mmHg and diastolic blood pressure (DBP) ≤95 mmHg)
2.4. Diabetes: Patients with insulin-independent diabetes mellitus adjusting fasting blood glucose <7.8 mmol/L (140 mg/dL) (BMI 27–29.9 kg/m^2^)
2.5. Hyperlipidaemia: Patients under adequate treatment after being diagnosed with hyperlipidaemia (BMI 27–29.9 kg/m^2^) or with measurements of total cholesterol of more than 236 mg/dL or triglycerides of more than 150 mg/dL at screening
3. Subjects who have agreed to a low-calorie diet during the trial
4. Patients who have provided signed written consent for the trialform for

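### The second main objective, a correlation between obesity and the Taeum constitution, cannot be answered in a sample where everyone is obese; it should be restated as exploratory and limited to the obese range

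*Protocol article*

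**What the plan says.** Study objectives lists two main objectives. The first is efficacy and safety; the second is "to detect the correlations between obese participants and the Taeum classification of Sasang constitutional medicine". Other sections word the second as a relation with obesity itself. The Background says "We also want to verify the correlation between obesity and Sasang’s Taeum constitution", and the Discussion paragraph of the Abstract says of the study that "it will provide evidence of correlation between obesity and Sasang constitutional medicine". The main Discussion names the same investigation as a distinctive feature of the trial.

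Table 1 (Inclusion criteria) offers two BMI routes. One is "2.1. BMI 30 kg/m^2^ or over". The other is BMI 27 to 29.9 for patients "who have more than one of the risk factors such as hypertension, diabetes, and hyperlipidaemia". The Background uses a lower cut-off for obesity: "The prevalence of obesity (body mass index (BMI) ≥25) in Korean adults is 30.6" per cent. Study design describes two arms, Euiiyin-tang and placebo, both drawn from this population.

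The Background also poses a separate treatment question. The constitution questionnaire (QSCCII) will be examined "to identify whether Euiiyin-tang has a significant effect for Taeum-in or not". It adds that "QSCCII was not considered as a primary outcome measure in the study, as it is not yet highly validated". Secondary outcome measurements says only that QSCCII responses will be assessed.

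**The concern.** A correlation between obesity and constitution needs people who differ in obesity, or an outside distribution of constitutions to compare with. The Background gives as its starting point that obesity is most prevalent among Taeum-in, which is a comparison across obese and non-obese people. The trial has only the obese side of it. A high share of Taeum among the volunteers could reflect the share in the general population, or who answers hospital advertisements, as much as any link with obesity.

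One of two main objectives, announced in the Abstract as a product of the trial, therefore has no supporting comparison. A statistical analysis plan cannot repair this, because the limit lies in the eligibility criteria and the arms. The objective also rests on an instrument that the Background itself calls not yet highly validated.

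The treatment question raises a smaller issue. A significant drug-placebo difference within Taeum-in shows that the drug works in that group. It does not show that the drug works better there than in other constitutions, which is what a constitution-specific benefit would mean.

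**Working it through.** **Step 1: the obesity correlation.** Let O = 1 for obese, T = 1 for Taeum, and p the share of Taeum in the sample. The lowest BMI admitted is 27 (Table 1) and the cut-off is 25 (Background), so O = 1 for everyone.

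- Var(O) = 1 × (1 − 1) = 0
- Cov(O, T) = E(OT) − E(O)E(T) = p − 1 × p = 0
- Correlation = 0/0, undefined

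An odds ratio fails for the same reason: it needs the Taeum share among non-obese people, and there are none. Sample size does not enter, so a larger trial would not help.

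**Step 2: what can be estimated.** Two quantities remain.

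- The share p among participants.
- The association of T with BMI (which has no upper limit in Table 1), body fat, waist and hip circumferences, waist-to-hip ratio and visceral fat (all in Secondary outcome measurements). This holds only for BMI of 27 or more and, between 27 and 29.9, only for women selected for risk factors.

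**Step 3: the plan's own sample size.** Inputs from Sample size: SD 3.9, difference 1.95 (effect size 0.5), two-sided 5%, 80% power, allocation 1:1, about 20% dropout. The article prints no unit for 3.9 and 1.95; kg is assumed.

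- m = 2 × (1.960 + 0.842)² / 0.5² + 1.960² / 4 = 63.75, rounded up to 64
- 64 / 0.80 = 80 per group, 160 in total

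The stated figure is reproduced. It covers the primary weight comparison only.

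**Step 4: precision of a treatment-by-Taeum interaction.** The Taeum share is not in the article, so p is varied from 0.3 to 0.7, taken as equal in both arms, with SD 3.9 in every cell. With N analysed in total:

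- SE = 3.9 × √(4/(Np) + 4/(N(1 − p)))
- Detectable with 80% power = (1.960 + 0.842) × SE
- 95% confidence interval half-width = 1.960 × SE

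N = 128 is 64 completers per arm. N = 160 is 80 per arm, as in the ITT dataset with LOCF (Efficacy assessment).

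| N | p | SE | Detectable (kg) | 95% CI half-width (kg) | Power if the interaction is 1.95 |
|---|---|---|---|---|---|
| 128 | 0.5 | 1.379 | 3.86 | 2.70 | 29% |
| 128 | 0.4 or 0.6 | 1.407 | 3.94 | 2.76 | 28% |
| 128 | 0.3 or 0.7 | 1.504 | 4.21 | 2.95 | 25% |
| 160 | 0.5 | 1.233 | 3.46 | 2.42 | 35% |
| 160 | 0.4 or 0.6 | 1.259 | 3.53 | 2.47 | 34% |
| 160 | 0.3 or 0.7 | 1.346 | 3.77 | 2.64 | 31% |

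Against the planned 1.95, the detectable interaction is 3.46/1.95 = 1.8 to 4.21/1.95 = 2.2 times as large. For 80% power at an interaction of 1.95, N = (2.802 × 3.9/1.95)² × 4/(p(1 − p)), which gives 503 evaluable participants at p = 0.5 and 599 at p = 0.3 or 0.7.

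**The case against.** The best defence of the second objective is its wording in Study objectives, which speaks of obese participants and can be read as an analysis within the sample. On that reading something useful is estimable. A reader might infer that the trial can report nothing but the share of Taeum; that goes too far, because degree of obesity and fat distribution vary and are measured. This part of the defence stands, and it points to the fix. It does not rescue the Abstract, Background and main Discussion, which speak of obesity itself.

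Could the BMI 27 to 29.9 group serve as a non-obese comparison? No. Table 1 itself calls these patients obese, they lie above the Background's cut-off, and they enter only with risk factors.

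On the treatment question, a reader might infer that the plan will test Taeum and non-Taeum participants separately and declare a Taeum-only effect when just the first test is significant. The article states no such procedure, names no subgroup test and makes no Taeum-only claim. With the same true effect of 1.95 in everyone, that pattern would arise in about 10% to 45% of trials as the assumed Taeum share goes from 30% to 70%. Those rates describe a hypothetical procedure and are not a property of this plan. Drug against placebo within Taeum-in is a valid randomised comparison for the question as literally worded.

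The lack of an interaction model in the article is likewise no fault, since a full protocol or analysis plan may contain one. Nor does it matter to any result that QSCCII is mentioned under the secondary outcomes.

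**Conclusion.** The concern holds for the obesity-constitution correlation: as worded in the Abstract, Background and main Discussion, it cannot be estimated from this trial. That conclusion needs no numerical assumption, only the eligibility criteria, the two arms and the article's own cut-off.

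For the treatment question, the conclusion is conditional. If a Taeum-specific benefit is meant, the interaction is the right contrast, and the trial could reliably detect only one about twice the planned main effect. This rests on an assumed Taeum share of 30% to 70%, equal SDs of 3.9, and a normal approximation. It can therefore only be exploratory.

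A reader might infer that the trial as a whole is compromised. The documents do not support that: randomisation, the primary endpoint, its sample size and its analysis do not depend on constitution, and QSCCII is expressly kept out of the primary outcome. This is a correction to one objective and to what the trial may conclude, to be made before results are reported. It is not a condition for the primary analysis.

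**What to change.** 1. Restate objective 2 along these lines: *to describe, as an exploratory aim, the distribution of Sasang constitution among participants and its association with BMI, waist and hip circumferences, body fat and visceral fat within this obese sample*.
2. Withdraw the claims of a correlation between obesity and constitution in the Abstract, Background and main Discussion, or restrict them in the same way.
3. State whether the Background's treatment question means an effect in Taeum-in or a Taeum-specific benefit. If the latter, fit one linear model for weight change at visit 5 with treatment, Taeum and their product. Report the product term as an estimate with a 95% confidence interval, label it exploratory, and do not rest the conclusion on significance within Taeum-in alone. Use the QSCCII classification obtained before randomisation, if there is one; the readable text does not give its timing.

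The cost is a change of wording and one additional model, which the t tests and repeated measures ANOVA named in Efficacy assessment do not already provide. QSCCII is already planned, so no new data collection is implied unless its timing has to change. With 149 of 160 participants recruited (Trial status), adding a non-obese group is not realistic, whereas these changes still are. The trial gives up a claim that it cannot support, and the interaction estimate will be imprecise, with a 95% interval of roughly ±2.4 to ±2.9 kg.

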### Recruitment

Subjects will be recruited through advertisements. Detailed information on the study including study duration, purpose of the study, eligibility criteria, and the intervention is posted on bulletin boards both inside and outside the hospitals, and patients who visit the trial site will do so voluntarily.

### Participants

#### Inclusion criteria

The inclusion criteria of the trial are provided in Table 1.

**Table 1 Tab1:** Inclusion criteria

Criteria for inclusion of participants
1. Women aged 18–65 years
2. Patients who have any of the following conditions:
2.1. BMI 30 kg/m^2^ or over
2.2. Obese patients, BMI 27–29.9 kg/m^2,^ who have more than one of the risk factors such as hypertension, diabetes, and hyperlipidaemia, and each of the conditions shall be subject to the following standards.
2.3. Hypertension: Patients under adequate treatment after being diagnosed with hyperlipidaemia (BMI 27–29.9 kg/m^2^) and with their blood pressure adjusted (satisfying all the conditions of systolic blood pressure (SBP) ≤145 mmHg and diastolic blood pressure (DBP) ≤95 mmHg)
2.4. Diabetes: Patients with insulin-independent diabetes mellitus adjusting fasting blood glucose <7.8 mmol/L (140 mg/dL) (BMI 27–29.9 kg/m^2^)
2.5. Hyperlipidaemia: Patients under adequate treatment after being diagnosed with hyperlipidaemia (BMI 27–29.9 kg/m^2^) or with measurements of total cholesterol of more than 236 mg/dL or triglycerides of more than 150 mg/dL at screening
3. Subjects who have agreed to a low-calorie diet during the trial
4. Patients who have provided signed written consent for the trialform for

#### Exclusion criteria

The exclusion criteria of the trial are provided in Table 2.

**Table 2 Tab2:** Exclusion criteria

Criteria for exclusion of participants
1. Patients with endocrine disease such as hypothyroidism, Cushing’s syndrome, etc., conditions that could affect patient weight
2. Patients with heart disease (heart failure, angina pectoris, and myocardial infarction)
3. Patients with uncontrolled hypertension (SBP >145 mmHg or DBP >95 mmHg
4. Patients with malignant tumour or lung disease
5. Patients with cholelithiasis
6. Patients with severe renal disability (serum creatinine (SCr) > 2.0 mg/dL)
7. Patients with severe liver disability (2.5 times higher than the maximum value in normal group on alanine transaminase (ALT), aspartate aminotransferase (AST), alkaline phosphatase (ALP))
8. Patients with insulin-independent diabetes mellitus, with fasting blood sugar more than 7.8 mmol/L (140 mg/dL)
9. Patients with narrow angle glaucoma
10. Patients with history of neurological or psychological disease or currently suffering from such diseases (schizophrenia, epilepsy, alcoholism, drug addiction, anorexia, bulimia, etc.)
11. Patients with history of stroke or temporary ischaemic cardioplegia
12. Patients with history or existence of eating disorder such as anorexia nervosa or bulimia nervosa, etc.
13. Patients with experience of medications that could have an effect on weight within last 3 months such as appetite suppressant, laxative, or oral steroid, thyroid hormone, amphetamine, cyproheptadine, phenothiazine, or medications affecting absorption, metabolism, and excretion
14. Patients under administration of central nervous system or central active weight reduction medications
15. Patients with experience of β-blocker or diuretic as hypertension medication within last 3 months
16. Forbidden treatments (insulin, hypoglycemic agent, antidepressant, antiserotonin agent, barbiturate, antipsychotic, medication abuse concerns)
17. Patients having difficulty with body measurements due to anatomical change such as resection
18. Patients with experience of surgical history for weight reduction; bariatric surgery, etc.
19. Patients judged unable to follow instructions of the trial by clinical trial investigators
20. Women of childbearing age who are pregnant, breastfeeding, planning a pregnancy, or who do not agree to use proper contraceptive methods (birth control pills, hormone implant, intrauterine device (IUD), spermicide, condom, abstinence, etc.). (Women of childbearing age refers to those within 2 years of menopause who have not had a hysterectomy, bilateral tubal ligation, bilateral oophorectomy, etc.)
21. Patients who have used other test products within the past month
22. Patients who have experienced a 10% weight reduction within the past 6 months
23. Those who decided to stop smoking within the last 3 months or who have an irregular smoking habit

### Subject withdrawal criteria

The subject withdrawal criteria are as follows: detection of eligibility violations; occurrence of a serious adverse event; subject has an acute reaction (such as allergy or shock) due to administration of the investigational product; detection of a systemic disease that was not discovered at the screening stage; less than 70% compliance; subject’s withdrawal of consent; use of any forbidden medication or treatment during the trial that could affect the study result; uncooperative subject; occurrence of other significant protocol violations; subject who cannot follow up; subject unable to progress because of worsening of pre-existing disease; investigator’s decision to terminate the process for the sake of the subject’s health. The participants who are withdrawn after randomisation will be followed up to examine outcomes.

### Sample size

The sample size calculation is based on weight change between baseline (visit 2) and after treatment (visit 5). The hypothesis is as follows:$$ {\mathrm{H}}_0:\updelta =\Delta 1\hbox{-} \Delta 2=0 $$
$$ {\mathrm{H}}_1:\updelta =\Delta 1\hbox{-} \Delta 2\ne 0 $$where Δ1 = Weight change between visit 5 and baseline in Euiiyin-tang group

Δ2 = Weight change between visit 5 and baseline in placebo control group.

In a study by Heymsfield et al. [23], the standard deviation (SD) in weight reduction of the groups is 3.9. We assume that both groups will have an equivalent SD. The effect size of this study is hypothesised to be 0.5 as the moderate effect. Consequently, the difference in weight change between groups is assumed to be 1.95. The allocation ratio is 1:1. The following formula is used to estimate the sample size [24]:$$ \mathrm{m}=\left(\frac{1+\psi}{\psi}\right)\kern0.24em \frac{{\left({\mathrm{z}}_{1\hbox{-} \frac{\upalpha}{2}}+{\mathrm{z}}_{1\hbox{-} \beta}\right)}^2}{\varDelta^2}+\frac{{{\mathrm{z}}^2}_{1\hbox{-} \frac{\upalpha}{2}}}{2\left(1+\psi \right)} $$where *m* = the sample size of one group$$ \uppsi =\mathrm{the}\;\mathrm{allocation}\;\mathrm{ratio} $$
$$ \upalpha =0.05,\upbeta =0.8 $$

After taking into account the dropout rate of approximately 20%, the sample size for each group is 80 participants, to allow the test to remain within 5% of the two-sided significance level and possess 80% statistical power. Therefore, the total sample size of this trial is 160.

